#### Data analyses

Generalised linear mixed effects models (GLMM) will be used to determine change on outcome measures. Primary analysis will compare measures at time one (baseline) and two (post-intervention), to identify fixed effects of the intervention. Potential clustering effects will be examined and accounted for at the school level. The model will include 2 main effects (Repeated measures effect of Time and Between subjects’ effect of Condition) and one two-way interaction Time*Condition). Gender effects will also be considered. With gender in the analyses, the model will have three main effects and corresponding two-way and three-way interactions. Secondary analyses will examine data from time 3 (follow-up) to see if the intervention condition has maintained hypothesised changes in dependent variables. We will also assess the proportion of within-group and between-group variance by calculating the Intra Class Correlation (ICC). As complex models can fail to converge, if we encounter convergence issues in our models, we may consider dropping the random effect accounting for the smallest proportion of between-group variance.

Mediation analyses will investigate whether body ideal internalisation, self-compassion and compassion for others mediate change in outcomes of body dissatisfaction and positive body image from T1 to T2 in the intervention condition. Moderation analyses will investigate whether appearance-related social media use, appearance teasing, gender, school type, baseline body appreciation, body dissatisfaction, psychological wellbeing and implementation quality moderate changes from T1 to T2.

Exploratory analyses will investigate the extent to which results are sensitive to floor effects which are common in universal body image interventions. We will conduct a mixed-effects regression model that includes participants who report moderate levels of body dissatisfaction (i.e., boys and girls who score 1.5 standard deviations below mean for body dissatisfaction of their respective genders).

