## Method

### Design

This study will use a parallel two-arm cluster randomised control trial (cRCT) with equal allocation of schools to intervention or waitlist control conditions (see Fig. 1). Teachers in schools assigned to the intervention condition will receive training and will deliver the BodyKind programme to students, while the waitlist control will receive classes as usual. This will be a pragmatic trial, conducted under ‘real world’ conditions i.e., in a school setting, with teacher-led delivery during class time over a four-week period (1 lesson each week). Outcomes will be measured at three time points (pre-, post- and two-month follow up). As per [54], a two-month follow up was selected to fit within the academic school year. Waitlist control schools will complete teacher training and the BodyKind programme after the completion of measures. This study received ethics approval from University College Dublin University (HS-22-71) and was retrospectively registered on 10/10/2023 on ClinicalTrials.gov, NCT06076993.

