### Participants

We aim to recruit a total of 600 students aged 15-17 years in Senior Cycle: Transition Year (a non-academically structured year in Irish secondary schools designed to facilitate the pursuit of alternative interests and self-discovery). An RMASS power analysis [55] based on parameters; small Cohen’s d effect size of .2, power .80, alpha .05, indicates that 504 students are required. A small effect size was selected in line with a meta-analysis of schools-based interventions for body image outcomes [14] which observed small effect sizes (d=.22 - .48) which despite being described as ‘small’ can have important real-world impact, particularly when scaled up across a whole school population [56]. To account for natural attrition and unanticipated events that reduce participant numbers (e.g., student absence due to illness) in cRCTs, we will recruit approximately 20% (*n=*100) more participants giving a total *N=*600. Given the variability in class size in Transition Year range in consent rates for active parental consent [57], and to guard against drop out at a cluster level we will recruit a minimum of 12 schools and a maximum of 26 schools with 1-2 fully qualified second-level teachers per school (range 12-52 teachers). Schools will be eligible if they are a second-level school in the Republic of Ireland that offers the Transition (TY) programme to students. Only data from full-time TY students aged 15-17 years (i.e., not exchange or short-term visiting students) will be included in analyses.

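### The plan names no school-by-time effect for the primary Time*Condition test, and its convergence rule could remove one; without it, students' changes are tested as independent in a school-randomised trial

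*Protocol article*

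**What the plan says.** All places are in the protocol article.

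- **Method, Design:** the trial is a "parallel two-arm cluster randomised control trial (cRCT) with equal allocation of schools to intervention or waitlist control conditions".
- **Data analyses:** the primary comparison is time one against time two. "The model will include 2 main effects (Repeated measures effect of Time and Between subjects’ effect of Condition) and one two-way interaction Time*Condition".
- **Data analyses, on clustering:** "Potential clustering effects will be examined and accounted for at the school level". No random effect is listed by name.
- **Data analyses, on convergence:** if models do not converge, the authors may drop whichever random effect explains least of the between-group variance. No term is exempt.
- **Data analyses, on the ICC:** an ICC will be calculated from the trial data. The text does not say whether it refers to outcome levels or to change.
- **Participants:** "we will recruit a minimum of 12 schools and a maximum of 26 schools". The sample size rests on "small Cohen’s d effect size of .2, power .80, alpha .05, indicates that 504 students are required", and "we will recruit approximately 20% (*n=*100) more participants giving a total *N=*600". No planning ICC is printed.
- **Background, hypothesis 7:** implementation quality may differ between schools and may affect how well the programme works.

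**The concern.** The treatment effect here is the difference between arms in mean change. The clustering that matters for it is clustering of change: whether students in one school move together from T1 to T2 because of their teacher, class climate, school events or timing in the term. A school effect that is the same at both times does not capture this, because it subtracts out of every student's change.

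The terms given in the article do not bring in a school-by-time effect. If one were fitted, it could well be the smaller of the two school-level variances, which makes it a likely candidate for removal under the convergence rule. An ICC of outcome levels would not reveal the problem.

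At stake are all three primary outcomes. Without the term, their confidence intervals would be too narrow and the chance of a false claim of effectiveness would exceed the stated alpha of .05, while the report could still say that clustering had been handled.

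**Working it through.** **Inputs from the article.** Alpha .05 (sidedness not stated; two-sided assumed here), N = 600, 12 to 26 schools, equal allocation by school, T1 against T2. Students per school: 600/26 = 23.1 and 600/12 = 50.

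**The plan's own figure.** The only computed figure is 504 students. A plain two-sample calculation at d = .2 and 80% power gives 786 in total (two-sided) or 620 (one-sided), so 504 is not reproduced that way. It is reached with an unprinted correlation over time, for example r = .60 with a factor 1 − r², or r = .68 with a factor 2(1 − r). RMASS needs inputs that the article does not print, so this does not show 504 to be wrong. It does mean that no ICC can be taken from the sample size section, and the values below are assumptions.

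**Step 1: what cancels.** With constant school and student effects,

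Y(school j, student i, time t) = fixed effects + u_j + b_ij + e_ijt,

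so the change is D_ij = time effect + interaction × condition + (e_ij2 − e_ij1). Both u_j and b_ij drop out. With two time points and balanced data, the interaction test is then a student-level two-sample t test on change. On four simulated data sets, the fitted mixed model and that t test gave p-values within .001 of each other (for example .0482 and .0487).

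Adding a school-by-time effect v_jt puts (v_j2 − v_j1) into D_ij. That is the term that carries school-level variation in change.

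**Step 2: type I error without that term.**

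DEFF = 1 + (m − 1) × ICC_change; type I error = 2 × [1 − Φ(1.96/√DEFF)].

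| ICC of change (assumed) | 26 schools of 23: DEFF | Type I error | 12 schools of 50: DEFF | Type I error |
|---|---|---|---|---|
| 0 | 1.00 | 5.0% | 1.00 | 5.0% |
| .01 | 1.22 | 7.6% | 1.49 | 10.8% |
| .02 | 1.44 | 10.3% | 1.98 | 16.4% |
| .05 | 2.10 | 17.7% | 3.45 | 29.1% |

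Simulation with 20,000 trials per setting agrees: 5.1%, 7.6%, 10.3% and 17.7% with 26 schools; 5.0%, 11.0%, 16.6% and 29.0% with 12.

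**Step 3: the same data with schools respected.** A t test on school-mean changes, with (schools − 2) degrees of freedom (24 or 10), rejects in 4.7% to 5.1% of simulated trials in every setting of the table.

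**Step 4: how an ICC of change can arise.** Assume an outcome ICC of .05, a within-student correlation of .6 and a correlation of .8 between a school's effects at T1 and T2.

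- School variance of change: 2 × .05 × (1 − .8) = .02.
- Student variance of change: 2 × .95 × (1 − .6) = .76.
- ICC of change: .02/.78 = .026, inside the range tabulated.

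**Step 5: the convergence rule.** Under the same assumptions the constant school variance is .05 × .8 = .04 and the school-by-time variance is .05 × .2 = .01. The term that the primary test needs is the smaller school-level one, so the rule as written could remove it.

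**The case against.** The strongest reply is that the article does not fix the faulty model. It never says that school enters only as a random intercept, and a school-by-time effect is also an adjustment at the school level. The convergence rule itself implies that more than one random effect is foreseen. The full list of random effects and the degrees-of-freedom method commonly stand in a statistical analysis plan, which is not shown here.

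The student effect is also inferred from the repeated-measures wording. Its presence decides the direction of the error. With a school intercept and no student effect, and assuming a correlation over time of .7 and a level ICC of .03, the test with 26 schools rejects only 0.04% to 1.5% of the time for an ICC of change from 0 to .05.

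All of this stands. A reader might infer that the protocol will test students as if they had been individually randomised, with a false-positive rate of 10% to 18%. The document supports neither statement: the model is not fixed that far, and any such rate rests on ICCs that the article does not give.

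Hypothesis 7 needs care too. Uneven implementation arises in the intervention arm and bears mainly on interval width when there is an effect. Inflation under no effect needs schools to differ in change for reasons present in both arms, such as teacher, class or timing.

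The reply does not dispose of the convergence rule. It is fixed in the article, exempts nothing, and would permit removal of the needed term from the primary test even if the authors intend to fit it.

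**Conclusion.** The point holds conditionally. If school is fitted only as a constant effect beside a student effect, or if a school-by-time term is dropped for non-convergence, the Time*Condition test ignores clustering of change. For an ICC of change between 0 and .05, the type I error is then 5% to about 18% with 26 schools of 23, and 5% to about 29% with 12 schools of 50. It stays at 5% only if schools do not differ in how they change.

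These figures assume equal school sizes, a two-sided 5% test and the stated ICCs of change, none of which the article supplies. The upper figures belong to the stated minimum of 12 schools; the Abstract and the randomisation section plan for 26. The change should be made, because the article's own rule leaves the validity of the primary test open and the remedy is cheap.

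**What to change.** In Data analyses, or in the statistical analysis plan, state that:

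1. The primary Time*Condition model includes a random school-by-time effect in addition to the school and student effects. A school-level analysis of mean change is an acceptable alternative.
2. The convergence rule may not remove the school-level terms. If the model does not converge, the fallback is the analysis of school-mean change.
3. The interaction is tested with school-based degrees of freedom, for example Kenward-Roger or Satterthwaite.
4. The ICC of change is reported as well as the ICC of level.
5. The same applies to the T3 contrast.

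This takes one or two sentences and one variance term, with no new data or participants. The cost is wider intervals, by about √DEFF. At an ICC of change of .02 that is √1.44 = 1.20 with 26 schools of 23 and √1.98 = 1.41 with 12 schools of 50, before the effect of fewer degrees of freedom. If schools do not differ in change, the widening is small.

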### Recruitment and randomisation

We will recruit students and teachers at the school level using 1.) Personal introductions to schools via our research partner, Educator School Centres Ireland’s (ESCI), who host continuing professional development (CPD) for teachers/schools on behalf of the Department of Education and Skills, 2.) Body Confident Schools webinar event for schools (a single online event for schools, hosted by ESCI & Jigsaw, The National Centre for Youth Mental Health), 3.) Advertisement on social media & website pages, 4.) Cold call invitations.

Schools will be selected on the basis of 1.) their expressed interest and 2.) their fit with recruitment criteria. Prior to randomisation, schools will be stratified based on school categorisation (e.g., urban/rural and single sex/coeducational) to ensure the gender and geographical location of participants in each treatment group is closely balanced. A stratified shortlist of 26 schools will be allocated using covariate-constrained randomisation, a type of minimisation randomisation, with the R statistical package cvcrand (https://cran.r-project.org/web/packages/cvcrand/cvcrand.pdf). Allocation will be constrained by a.) the number of boys and b.) the number of girls in TY in each school, and c.) the school’s location categorisation (urban/rural). Shortlisted schools registering interest that decline to participate after initial contact will be replaced by schools on the waitlist based on minimisation, or replacement by same category method. Given the nature of the study, blinding participants to their condition will not be possible.

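### The primary Time-by-Condition model is in effect a change-score comparison: it does not condition on baseline, omits the allocation variables, and may leave school clustering out of the test

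*Protocol article*

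**What the plan says.** The Data analyses section of the protocol article sets the comparison: "Primary analysis will compare measures at time one (baseline) and two (post-intervention), to identify fixed effects of the intervention". It then lists the fixed effects: "The model will include 2 main effects (Repeated measures effect of Time and Between subjects", the second being Condition, plus the Time-by-Condition interaction. Gender is to be considered as well, in a fuller form: "With gender in the analyses, the model will have three main effects and corresponding two-way and three-way interactions". On schools it says: "Potential clustering effects will be examined and accounted for at the school level". It does not say whether the school effect is constant over time or may differ between surveys. It also allows the random effect with the smallest share of between-group variance to be dropped if a model fails to converge.

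Recruitment and randomisation describes the allocation. Beforehand, "schools will be stratified based on school categorisation (e.g., urban/rural and single sex/coeducational"; then "Allocation will be constrained by a.) the number of boys and b.) the number of girls in TY in each school", with urban/rural location as the third constraint. None of these school-level variables is in the primary model. School type and the baseline scores appear in the analysis only as moderators: "gender, school type, baseline body appreciation, body dissatisfaction, psychological wellbeing and implementation quality moderate changes from T1 to T2".

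**The concern.** Two features of the stated model deserve attention.

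First, each student has a baseline score, but the model uses it only as the first of two outcome waves. With a free Condition main effect, the interaction is the difference in mean change. If students were independent, that contrast would never be more precise than one that conditions on baseline, for any r below 1. The allocation variables, which would normally accompany a direct model of the post-intervention score, are also absent.

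Second, anything constant within a school over time drops out of a change. A time-constant school intercept would therefore appear in the model and yet do nothing for the standard error of the tested term. At stake are some precision in a trial with 12 to 26 schools and, on one reading of the clustering sentence, the type I error rate of the primary test.

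**Working it through.** **Inputs from the article.** Two waves in the primary analysis and the fixed effects above (Data analyses). d = 0.2, power .80, alpha .05, 504 students required, 600 to be recruited, 12 to 26 schools (Participants). **Assumed, because the article gives none:** pre-post correlation r among students, ICC, and the correlation ρc between a school's effect at T1 and at T2.

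**1. The plan's own figure.** Without a correlation, n per arm = 2(1.96 + 0.84)²/0.2² = 393, so 786 in all; one-sided it is 310 per arm, 620 in all. Neither is 504. The ratio 504/786 = .641 would follow from baseline adjustment at r = .60 (1 − .36 = .64) or from a change score at r = .68 (2 × .32 = .64), both without clustering. Neither value is printed. So r cannot be recovered from 504, and the mismatch does not show 504 to be wrong. It serves below only as a scale.

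**2. What the model tests.** A mixed model with school and student intercepts, fitted to simulated complete two-wave data, gave a Time-by-Condition estimate of 0.0435 with SE 0.0681. The two-sample test on change scores gave the same values to three significant figures.

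**3. Precision, ignoring clustering.** Per unit variance, a change score has variance 2(1 − r) and a baseline-adjusted score 1 − r². The ratio is (1 + r)/2 and the loss is (1 − r)/2.

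| r | ratio | loss | equivalent of 504 | equivalent of 600 |
|---|---|---|---|---|
| .5 | .75 | 25% | 378 | 450 |
| .6 | .80 | 20% | 403 | 480 |
| .667 | .833 | 16.7% | 420 | 500 |
| .7 | .85 | 15% | 428 | 510 |
| .8 | .90 | 10% | 454 | 540 |

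Simulation at 252 per arm gave ratios of .746, .838 and .903 at r = .5, .667 and .8, which agrees.

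**4. Precision, with clustering.** The comparison is a post-intervention model with student baseline and a school intercept, against the change score, at r = .68, ICC .01 to .05 and 12 to 26 schools. Simulated variance ratios were mostly .81 to .92. Single cases at ρc = .9 were .85 (26 schools, ICC .01), .92 (26 schools, ICC .05) and .96 (12 schools, ICC .03 or .05). When school effects were nearly or fully stable, with 12 schools or with ICC .05, the ratio was about 1.0 to 1.2: no gain, or a loss.

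**5. Allocation variables.** Urban/rural location and the counts of boys and girls do not change between waves, so their main effects cancel from the interaction. In one simulated 12-school data set with a strong school covariate, adding it left the Time-by-Condition estimate (−0.378) and SE (0.1221) unchanged.

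**6. Clustering in the tested term.** The ICC of the change score is

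ICCΔ = ICC(1 − ρc) / [ICC(1 − ρc) + (1 − ICC)(1 − r)].

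A test whose only school term is a constant intercept ignores the design effect 1 + (m − 1)ICCΔ, where m is students per school. Worked case with 12 schools, m = 504/12 = 42, ICC .05, ρc = .8, r = .68: ICCΔ = .010/(.010 + .304) = .032; design effect 1 + 41 × .0318 = 2.31; effective critical value 1.96/√2.31 = 1.29; rejection rate 20%.

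| schools | ICC | ρc = .8 | ρc = .6 |
|---|---|---|---|
| 26 (m = 19.4) | .02 | 8% | 10% |
| 26 | .05 | 12% | 18% |
| 12 (m = 42) | .02 | 11% | 17% |
| 12 | .05 | 20% | 30% |

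At ρc = 1, ICCΔ = 0 and the rate is 5%. Simulation over a range of such settings gave about 5% to 29%. A school-level test of the baseline-adjusted score held 4.5% to 5.4% in the tabulated settings.

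**The case against.** A two-wave Time-by-Condition mixed model is valid and common, gives an unbiased estimate, and matches the first hypothesis, which is about change from before to after. That stands: the baseline point concerns efficiency, not bias. Gender is not ignored either; there is a version of the model that includes it. Covariate lists are often left to an analysis plan, but here the article names the fixed effects outright, so the choice can be discussed.

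A reader might infer that a sixth of the sample is wasted, or that power would rise from 80% to 86%. The documents do not support either. The first needs r near .67 and the second r = .68, both without clustering, and no r is given. Nor does either figure come from the omitted allocation variables; both concern baseline handling alone.

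A reader might also infer that leaving out those variables makes the present standard errors too wide. For this contrast it does not, by step 5. Precision would be lost only if they predicted change, which nothing in the article shows. They matter once the post-intervention score is modelled directly.

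The efficiency gain from baseline adjustment is also not guaranteed, by step 4. With 12 schools, ICC .05 and fully stable school effects, one simulated ratio was 1.15 against the replacement model. That objection stands and limits the claim.

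**Conclusion.** The point holds as a recommendation, not as a fatal defect. The stated primary model is a change-score comparison that does not condition on baseline and leaves out the allocation variables. The precision cost is 25% to 10% for r of .5 to .8 if clustering is ignored. It is usually about 5% to 19% at r = .68 with clustering, and may be nil or negative with few schools and very stable school effects. All of these rest on assumed correlations and ICCs.

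The stronger reason to act is clustering, and it is conditional. If the school term is only a constant intercept and school effects move between surveys, the primary test is anti-conservative. Under the assumed values in the table, rejection is 8% to 30% at a nominal 5%. A reader might infer that the trial's test is certainly inflated. The article does not say so: it promises to account for schools without giving the form, and a school-by-time effect would remove the problem. What it does is name no such term while allowing a random effect to be dropped.

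**What to change.** Make the primary model the T2 outcome on Condition, baseline outcome, student gender and urban/rural location, with a school random intercept that is retained whatever its estimated size, and small-sample degrees of freedom. Add the school-mean baseline if the number of schools allows. Add the counts of boys and girls only if the schools are near 26, since those counts overlap heavily with single-sex status.

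Keep Time-by-Condition as a sensitivity analysis, with a school-by-time random effect. Leave the gender interactions in the moderation model, so that the primary effect stays the overall one. Exempt the school term from the convergence rule.

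The cost is wording; all the variables are already to be collected or are known at allocation. The downside is a few school-level degrees of freedom, and little or no gain in precision if about 12 schools take part and their effects are highly stable.

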**Methods:**

We aim to recruit 600 students aged 15-17 years in Transition Year (4^th^ year) across 26 second-level schools in Ireland. Using minimisation, schools will be randomly assigned to receive BodyKind (intervention condition, *n=*300) or classes as usual (waitlist control, *n=*300). Teachers in intervention groups will receive training and deliver the programme to students over four weeks, at a rate of one lesson per week. Primary outcomes of body appreciation, body dissatisfaction and psychological wellbeing and secondary outcomes of self-compassion, compassion for others, body ideal internalisation, social justice motives and appearance-based social media use will be assessed at pre-, post- and 2 month follow up. Mediation and moderation analyses will be conducted to identify how and for whom the intervention works best. An implementation evaluation will assess the quality of programme implementation across schools and how this may influence intervention outcomes. Waitlist control schools will receive the programme after the 2-month follow up.

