In addition to examining effectiveness, best practice guidelines in school-based research increasingly emphasise the importance of conducting implementation evaluations to assess how well programmes are delivered in schools and if programmes are delivered as intended [49, 51, 52]. Implementation evaluations are essential for providing insights into factors that may lead to a programme’s success or failure [51]. They can also inform efforts to guide sustainable delivery of programmes in schools. Thus, a mixed methods evaluation of implementation quality will be conducted to understand ‘why’ programme outcomes were observed and to inform efforts to optimise programme delivery in schools in the future. Aligning with previous studies [52, 53], the quality of implementation of BodyKind in schools will be assessed across four key implementation dimensions: (i) dosage, (ii) adherence, (iii) quality of delivery, and (iv) participant responsiveness.

This study will be the first to implement a cRCT design and implementation evaluation to examine BodyKind – an innovative, gender-inclusive, culturally sensitive programme designed to improve adolescents’ body image and psychological wellbeing. This research is anticipated to provide novel contributions to school-based body image intervention work.

We hypothesise that 1.) Compared to participants in the waitlist control, participants who receive the BodyKind programme will experience statistically significant increases in a.) body appreciation, psychological wellbeing, self-compassion and compassion for others and other’s bodies, social justice motivations and b.) significant decreases in body dissatisfaction and body ideal internalisation from pre- to post-intervention. 2.) Changes will be maintained in intervention groups at a 2-month follow up. 3.) Changes in body appreciation and body dissatisfaction will be mediated by self-compassion, compassion for others and body ideal internalisation. We make no a-priori assumptions about the directionality of mediation effects. 4.) Changes in body appreciation, body dissatisfaction and psychological wellbeing will be moderated by appearance-related social media use, appearance teasing, gender, baseline body appreciation, body dissatisfaction, psychological wellbeing and implementation quality. We make no a-priori assumptions about the directionality of moderation effects.

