### Strengths & limitations

Strengths of the proposed study include the rigorous cluster randomised control design, adherence to CONSORT guidelines [89] and 2-month follow up which will enable us to evaluate immediate and sustained intervention effects in a real-life school setting. This study also builds on pilot work both in the USA and Ireland [46] which evaluates a version of the programme culturally adapted for the Irish context and will contribute to the continuum of evidence in accordance with the British Medical Council’s Guidelines on the Design and Evaluation of Complex Interventions [47]. This study is also strengthened by the diverse range of schools it is seeking to recruit (i.e., diverse school type, size and geographical spread) which will improve generalisability of study findings. Additionally, the inclusion of coeducational (mixed) and single sex schools will enable us to assess if there are any differences in how the programme is received in mixed versus single sex groups, which is an important consideration for body image intervention programmes, and especially for this programme which is one of the first to adopt a more gender-inclusive approach [17]. In light of calls within the body image and public health fields to develop school-based interventions that are scalable and can be sustainably delivered via community providers [36, 45], the teacher-led delivery and inclusion of the mixed methods implementation evaluation are particular strengths of this study. Implementation evaluations are not routinely conducted in body image intervention work, and so by examining factors influencing implementation quality according to students and teachers, in addition to assessing mediators and moderators of this multicomponent body image programme, this study aims to provide important insights that can inform future body image intervention work.

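### The two-month follow-up is framed as maintenance within the intervention arm; the between-arm contrast at follow-up, which the design allows, is not stated

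*Protocol article*

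**What the plan says.** Write T1, T2 and T3 for baseline, post-intervention and two-month follow-up.

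- **Hypotheses (end of Background).** Hypothesis 1 covers pre to post and names the comparator: "Compared to participants in the waitlist control, participants who receive the BodyKind programme will experience statistically significant increases". Hypothesis 2 does not: "Changes will be maintained in intervention groups at a 2-month follow up".
- **Data analyses.** "Primary analysis will compare measures at time one (baseline) and two (post-intervention), to identify fixed effects of the intervention". The model has main effects of Time and Condition "and one two-way interaction Time*Condition", with clustering handled at school level. Follow-up comes later in the same paragraph: "Secondary analyses will examine data from time 3 (follow-up) to see if the intervention condition has maintained hypothesised changes in dependent variables".
- **Design and Abstract.** "Outcomes will be measured at three time points (pre-, post- and two-month follow up"), in a two-arm trial. "Waitlist control schools will receive the programme after the 2-month follow up". The Teacher training section adds that waitlist teachers are trained only once data collection has ended.
- **Strengths & limitations.** The follow-up is said to allow the team to "evaluate immediate and sustained intervention effects".

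No T3 test, comparator, margin or definition of *maintained* is given.

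**The concern.** A sustained intervention effect is a difference between randomised arms at the later time. Hypothesis 2 and the T3 sentence instead ask what happened in the intervention arm. Students in that arm grow older, move to another part of the school year and answer the same questionnaire a third time, whether or not the programme has a lasting effect. The control arm goes through the same things, which is why it is needed at T3.

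Followed as worded, the analysis could mislead in both directions. The intervention arm could hold its T2 level while the controls catch up, so that no effect remains but the change looks maintained. Or both arms could fall together, so that the effect persists but looks lost. The T3 analysis is the only basis for the article's claim about sustained effects.

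**Working it through.** **1. The passages side by side**

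| | T1 to T2 | T3 |
|---|---|---|
| Hypothesis | 1: against the waitlist control | 2: intervention groups only |
| Analysis | Time, Condition, Time × Condition | whether the intervention condition maintained its changes |
| Control status | untreated | untreated, programme given afterwards |

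Hypothesis and analysis agree in dropping the comparator at T3, so this is not a slip in a single sentence. The design nevertheless supplies a concurrent control.

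**2. Why a within-arm answer is not enough**

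Take mean change from T1 in SD units, using the planning effect of 0.2 (Participants section). These are invented patterns.

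| Pattern | Intervention T2, T3 | Control T2, T3 | Between-arm T2, T3 |
|---|---|---|---|
| Controls catch up | 0.2, 0.2 | 0, 0.2 | 0.2, 0 |
| Both fall | 0.2, 0 | 0, −0.2 | 0.2, 0.2 |

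The intervention column gives the wrong answer on durability in both rows.

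**3. Illustration of size**

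The article has no T3 figure to reproduce. Inputs:

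- From the article: 504 students required and equal allocation of schools, taken here as 504 / 2 = 252 per arm. The figure 504 cannot be checked from the stated inputs alone: d = 0.2, power 0.80 and two-sided alpha 0.05 give 786 for a simple two-group comparison. Nothing here depends on whether 504 is right.
- Assumed: correlation between two times r = 0.5 to 0.8, and variance inflation for clustering DE = 1 to 2. The article gives neither.

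Standard error of a within-arm change: SE = sqrt(2(1 − r) × DE / n).

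- r = 0.8, DE = 1: sqrt(0.4 / 252) = 0.040
- r = 0.6, DE = 1: sqrt(0.8 / 252) = 0.056
- r = 0.5, DE = 2: sqrt(2 / 252) = 0.089

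*(a) Suppose maintained meant a significant T1-T3 gain within the arm.* With no programme effect and a drift of 0.1 SD in both arms, P = Φ(0.1 / SE − 1.96). This is 0.71, 0.43 and 0.20 for the three cases. The between-arm contrast has expectation zero and shows a false benefit with probability 0.025.

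*(b) Suppose maintained meant no significant T2-T3 decline.* If half of a 0.2 SD effect is lost, P = 1 − [Φ(0.1 / SE − 1.96) + Φ(−0.1 / SE − 1.96)]. This is 0.29, 0.57 and 0.80. If the whole effect is lost, it is 0.001, 0.056 and 0.39.

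**4. Precision of the between-arm contrast**

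Its SE is larger by sqrt(2): 0.056, 0.080 and 0.126. The 95% half-widths (1.96 × SE) are 0.11, 0.16 and 0.25 SD. Power for a true 0.2 SD difference in change, Φ(0.2 / SE − 1.96), is 0.94, 0.71 and 0.36. The contrast asks the right question but may be imprecise, so the interval matters more than a verdict of maintained or lost.

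**The case against.** The strongest reply is that the T3 sentence sits in the paragraph that sets out the Time × Condition model and names no other model. It speaks of hypothesised changes, and hypothesis 1 defines those against the waitlist. A maintained hypothesised change could then mean a maintained between-arm difference. This reading is possible, but it is stated nowhere, and hypothesis 2 points the other way by naming only the intervention groups.

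A second reply is that this is a secondary analysis in a journal article, and that the exact contrast and the meaning of *maintained* can be left to an analysis plan. That holds for the missing definition, which is not a fault by itself. It does not settle the main point: the stated question is a one-arm question, and an analysis plan that followed it faithfully would keep it.

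Two stronger readings are tempting and should not be made. A reader might infer that the plan treats a non-significant decline as maintenance. No sentence gives that or any other decision rule; case (b) in the working is one conceivable rule, not the plan's. A reader might also infer that control data at T3 will be ignored. The article does not say so, and the planned model could be extended to T3.

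**Conclusion.** The point holds as a matter of framing. Hypothesis 2 and the T3 analysis ask about maintenance within the intervention condition and do not state the between-arm contrast at T3, although the waitlist is still untreated then. A within-arm answer could not support the claim of sustained effects. That conclusion rests on the wording and the design alone.

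The probabilities are illustrations. They depend on decision rules that the article does not contain, on n = 252, and on assumed r = 0.5 to 0.8 and variance inflation of 1 to 2. The spread in case (b), 29 to 80% when half the effect is lost, shows that no single figure should be quoted. For example, r of about 0.68 without clustering would give 42 to 49% for 300 down to 252 students, but nothing in the article supports that choice.

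This is a free improvement to a secondary analysis. The T1-T2 primary comparison is not affected.

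**What to change.** 1. Restate hypothesis 2 as a difference between arms at T3.
2. Fit T1, T2 and T3 for both arms in the planned mixed model, with Time as a three-level factor, Condition, their interaction and school clustering.
3. Make the T3 Condition contrast, that is the difference between arms in T1-T3 change, with its 95% confidence interval, the follow-up test.
4. Report the T2-to-T3 change in the between-arm difference with its interval as the description of durability. If the word *maintained* is kept, define it in advance on this between-arm scale.

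The cost is wording only, since the design already provides for T3 measurement while the waitlist is untreated. The between-arm interval will be wider than a within-arm one, and the report should say so.
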